#### Data analysis

The effectiveness of the weight gain prevention guideline will be analyzed after 6 months (short term) and after 18 months (long term) by means of multilevel analyses. Multilevel analyses accounts for the clustering of observations of workers within the same OP, as well as repeated measurements within one worker. Due to randomization at the OP level, short term data will be analyzed with two levels: 1. worker and 2. OP. Long term data will be analyzed with three levels: 1. time (3 follow-up measurements at 6, 12 and 18 months), 2. worker and 3. OP. Both crude and adjusted analyses will be performed. The multilevel analyses using the follow-up measurement (i.e. 6 months) as dependent variable will be adjusted possible confounders such as, gender, age and education. These variables will also be checked for effect modification. The long-term effect of the intervention will be analyzed using all three follow-up measurements (i.e. 6, 12 and 18 months) adjusted for possible confounders. Effect modification is checked. All statistical analyses will be performed according to an intention-to-treat principle. The investigator analysing the data is blinded to the randomization. A two tailed significance level of p < 0.05 is considered statistically significant. Analyses will be performed with SPSS 15.0 (SPSS Inc. Chicago, Illinois, USA) and MLwiN for multilevel statistical analyses.

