**Methods:**

Following the guideline development protocol of the Netherlands Society of Occupational Medicine and the Intervention Mapping protocol, the guideline was developed based on literature, interviews with relevant stakeholders, and consensus among an expert group. The guideline consists of an individual and an environmental component. The individual component includes recommendations for occupational physicians on how to promote physical activity and healthy dietary behavior based on principles of motivational interviewing. The environmental component contains an obesogenic environment assessment tool. The guideline is evaluated in a randomised controlled trial among 20 occupational physicians. Occupational physicians in the intervention group apply the guideline to eligible workers during 6 months. Occupational physicians in the control group provide care as usual. Measurements take place at baseline and 6, 12, and 18 months thereafter. Primary outcome measures include waist circumference, daily physical activity and dietary behavior. Secondary outcome measures include sedentary behavior, determinants of behavior change, body weight and body mass index, cardiovascular disease risk profile, and quality of life. Additionally, productivity, absenteeism, and cost-effectiveness are assessed.

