#### Study population

OPs were recruited through a direct mailing by the Netherlands Society of Occupational Medicine to their member registry. OPs providing services to one or more companies of medium to large size (> 100 workers) and conducting preventive medical examinations were eligible to participate. OPs invited employees to participate via their usual channels (written letter, intranet, face-to-face in consultation hours). Inclusion criteria were: 1. unhealthy physical activity and/or dietary behavior and/or overweight, 2. currently not being on sick leave for 21 days or longer, 3. able to complete a Dutch questionnaire and 4. having signed an informed consent form. Unhealthy physical activity was defined as workers who do not meet physical activity guidelines [57]. Unhealthy dietary behavior was defined as workers who do not meet the Dutch national dietary guidelines for fruit- and vegetable consumption and fat [58]. Overweight and obesity were defined by a waist circumference larger than 94 cm and 102 cm respectively for men and larger than 80 cm and 88 cm respectively for women [59]. Obese workers could additionally be referred to the Dutch guideline for treatment of Obesity [60]. Workers were excluded when pregnant or in case a disease or condition was present which made physical activity impossible.

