#### Sample size

The sample size was calculated according to the number of cases needed to identify an effect on waist circumference. Waist circumference was chosen over BMI as it is a more sensitive indicator of abdominal fat mass [61]. A previous study indicated that a difference in waist circumference of 1,5 cm between the intervention and control condition may be clinically relevant [43]. In an intention-to-treat analysis, 175 workers per condition are needed to detect a relative difference of 1,5 cm (standard deviation 4,5 cm) in waist circumference with a power of 80% and an alpha of 5%. As workers are clustered within OPs we adjusted for dependence of measurements with an intraclass correlation of 0.20. Taking a loss to follow-up of 20-40% into account among workers and OPs until the final measurement, the initial study population should consist of approximately 300 workers among 10 OPs in each study group (figure 4).

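### Neither multilevel model specifies the baseline value of its outcome as a covariate, and neither the crude nor the adjusted analysis is named as primary

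*Protocol article*

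**What the plan says.** The Data analysis section of the Protocol article describes two models.

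- Short term: "The multilevel analyses using the follow-up measurement (i.e. 6 months) as dependent variable will be adjusted possible confounders such as, gender, age and education".
- Long term: "The long-term effect of the intervention will be analyzed using all three follow-up measurements (i.e. 6, 12 and 18 months) adjusted for possible confounders", with the levels given as "1. time (3 follow-up measurements at 6, 12 and 18 months), 2. worker and 3. OP".

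In both, the dependent variable is the follow-up value. Baseline is not among the repeated outcomes of the long-term model, and no change score is defined. Only the Economic evaluation section speaks of change in waist circumference. The Data analysis section adds "Both crude and adjusted analyses will be performed" and does not say which of the two carries the conclusion.

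The baseline values exist. The Abstract states "Measurements take place at baseline and 6, 12, and 18 months thereafter". The Sample size section states "175 workers per condition are needed to detect a relative difference of 1,5 cm (standard deviation 4,5 cm" but not whether that SD is of waist level, of change, or of values adjusted for baseline. According to Study design and Study population, OPs were randomised before the baseline measurement and then invited workers through their own channels. The Discussion lists non-standardised recruitment as a limitation.

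**The concern.** For a continuous outcome measured before and after, the baseline value is usually the strongest predictor of the follow-up value. An analyst who follows the text literally would leave it out of every model.

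Two features of this design make that costly. Only 10 OPs per arm are randomised, so chance differences in baseline waist between arms can be large relative to 1.5 cm. In addition, workers are recruited by OPs who already know their allocation, so the arms may differ systematically. Chance differences widen the interval; differential recruitment can bias the estimate. Baseline adjustment deals with the first and reduces the second.

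With a crude and an adjusted result both planned and neither designated, the choice between them could also be made after the results are seen.

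**Working it through.** **1. The plan's own figure.** Inputs (Sample size and Data analysis): difference 1.5 cm, SD 4.5 cm, power 80%, two-sided alpha 5%, ICC 0.20.

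- Without clustering: n = 2 × (1.96 + 0.84)² × (4.5/1.5)² = 2 × 7.849 × 9 = 141.3, so 142 per arm, not 175.
- With 175 workers over 10 OPs (17.5 each): design effect 1 + 16.5 × 0.20 = 4.3, and 142 × 4.3 gives 611 per arm.
- The stated 175 matches neither. The later step does reproduce: 175/(1 − 0.40) = 292, about 300.

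This mismatch is a separate sample-size problem, and baseline adjustment does not explain it.

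**2. Variance removed by baseline adjustment.** If r is the baseline-to-follow-up correlation and is the same at worker and OP level, the residual variance is (1 − r²) times the unadjusted variance. The documents give no r. In the model that already contains gender, age and education, r means the correlation remaining after those covariates.

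| r | share removed, r² |
|---|---|
| 0.5 | 25% |
| 0.58 | 34% |
| 0.8 | 64% |
| 0.9 | 81% |

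The 0.58 row borrows the SQUASH reliability from the Physical activity section as a rough guide for that outcome. More than half is removed only when r exceeds about 0.71.

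**3. Dependence on the OP level.** With ICC 0.20 and 17.5 workers per OP, the variance of an OP mean is proportional to 0.20 + 0.80/17.5 = 0.2457, and 0.20/0.2457 = 81% of it lies between OPs. The proportion left after adjustment is [0.20(1 − r_OP²) + 0.80(1 − r_worker²)/17.5]/0.2457. With worker-level r = 0.8:

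- OP-level r = 0: 88% remains
- OP-level r = 0.5: 68% remains
- OP-level r = 0.8: 36% remains

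**4. Plausible chance imbalance in baseline waist.** SE = SD × √(2 × [1 + 16.5 × ICC]/175). The level SD and the baseline ICC are assumptions.

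| SD of level | baseline ICC | SE | P(difference ≥ 1.5 cm) |
|---|---|---|---|
| 4.5 cm | 0.05 | 0.65 cm | 2% |
| 4.5 cm | 0.20 | 1.00 cm | 13% |
| 10.06 cm | 0.05 | 1.45 cm | 30% |
| 10.06 cm | 0.20 | 2.23 cm | 50% |

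An imbalance carries over to follow-up in proportion to r. With r equal at both levels and equal variances, 1.5 cm at baseline becomes 0.75 cm at r = 0.5 (0.5 × 1.5) and 1.2 cm at r = 0.8 (0.8 × 1.5).

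**5. Why the meaning of 4.5 cm matters.** Workers per arm for 80% power, before clustering, with equal variances at both times. If 4.5 cm is the SD of change, the level SD is 4.5/√(2(1 − r)).

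| r | 4.5 = change: follow-up only / baseline-adjusted | 4.5 = level: follow-up only / baseline-adjusted |
|---|---|---|
| 0.5 | 142 / 106 | 142 / 106 |
| 0.8 | 354 / 128 | 142 / 51 |
| 0.9 | 707 / 135 | 142 / 27 |

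If 4.5 cm is the residual SD after baseline adjustment, the follow-up-only model needs 189, 393 or 744 per arm at these three values of r, against 142 adjusted.

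**The case against.** The strongest reply is that silence is not exclusion. The short-term confounder list is introduced as examples and the long-term list is not given at all. This is a journal article, and the final covariate list may stand in an SAP that is not shown. That is correct: a reader might infer that the models omit baseline, but the text supports only that baseline is not specified. What remains is that the section fixes the dependent variable, the levels and example covariates, leaves out the most obvious one, and plans a crude model that by definition contains none.

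Three stronger readings are tempting and do not hold.

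- *Most of the precision is lost.* This needs r above about 0.71 at both levels. It is plausible for waist, but not shown for self-reported activity or diet.
- *Baseline imbalance passes in full into the effect estimate as bias.* It passes in proportion to r. Under randomisation of OPs the chance part is sampling variance, which a valid multilevel standard error already reflects. Only recruitment after allocation could bias.
- *4.5 cm cannot be an SD of waist level, so the sample size must assume baseline adjustment.* The overweight and obesity cut-offs, "larger than 94 cm and 102 cm respectively for men and larger than 80 cm and 88 cm respectively for women", differ by 14 cm between the sexes, which in a 50:50 sample would alone give an SD of 7 cm. But that treats cut-offs as population means, and gender is the first covariate named. With assumed total SDs of 8 and 12 cm, the SD within gender would be √(64 − 49) = 3.9 cm and √(144 − 49) = 9.7 cm. The first is below 4.5 cm, so a gender-adjusted level SD cannot be ruled out.

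Nor should the low power under clustering be charged to this point. At 175 per arm, SD 4.5 cm and ICC 0.20, the effective size is 175/4.3 = 40.7 per arm and power is about 32%. That comes from the missing design effect, an error in the stated calculation whichever model is used.

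**Conclusion.** The point stands as a specification gap with a real cost. Followed as written, both models give a less precise estimate, more exposed to baseline imbalance, than the collected data allow, and the basis for the conclusion is left open between two analyses.

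The size depends on r, on the level SD and on the baseline ICC, none of which the documents give. For waist, a high r is a reasonable assumption, and the gain could then exceed half the variance, provided OP means track over time as well as individual values do. For activity, about a third is a fair guide. For diet, the documents offer no basis for a figure. An imbalance of 1.5 cm or more ranges from unlikely (2%) to an even chance (50%) across the assumptions shown. The defect and its remedy do not depend on where in these ranges the truth lies.

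**What to change.** In the Data analysis section:

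1. Include the baseline value of the same outcome as a covariate in both the 6-month and the long-term models, for every primary outcome, alongside gender, age and education.
2. Name this baseline-adjusted model as the primary analysis and the crude model as supportive.

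In the Sample size section, state whether 4.5 cm is the SD of waist level, of change, or of baseline-adjusted values.

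Adding the OP mean of the baseline value is optional; it lets the OP-level relation differ from the worker-level one. The change costs a sentence or two and no new data, and should be made before the analysis begins. The treatment of ICC 0.20 in the sample size needs its own correction.

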In total, 5 counselling sessions are planned. During the first session, motivation for change is addressed. After 3 weeks a second session takes place in which goals are evaluated and updated. To enhance motivation and adherence to the personal goal behaviors, a third and fourth session are planned after 6 and 12 weeks. Due to time issues these two sessions can be by phone rather than face-to-face. Again, goals are evaluated and eventually updated. At the end of the intervention period after 6 months, a final counselling session will focus on the goals that have or have not been achieved, and on maintenance of healthy behavior.

Ultimately, the aim of the guideline is to incorporate attention for weight gain prevention in the company's health policy, which is supported by all relevant stakeholders (evaluation and maintenance, *section c*). Interviews among employers and employees revealed that an evaluation and/or maintenance plan for health initiatives are rarely exist. This section was therefore addressed separately in the guideline. Regarding prevention at the environmental level, the guideline recommends to evaluate to what extent the health policy is carried out after 6 months. In case the health policy is not or (only) partly implemented, possible reasons and barriers should be discussed. In order to maintain attention for the health policy, this issue should be addressed at least once a year in a meeting with the employer and the workers' representative council. Additionally, ongoing efforts should be made to evaluate risk factors that may induce relapse.

With respect to prevention at the individual level, short term goals should be evaluated after 12 weeks. When goals are reached, the OP is asked to compliment the employee on this achievement and to discuss long-term goals for maintaining this healthy behavior. Goals that have not been reached are discussed and the action plan is revised. Additionally, an active provision of information should be realized in order to maintain attention for healthy behavior, for example during other consultations than preventive medical examinations.

According to the commentary phase of the Netherlands Society of Occupational Medicine protocol, the draft guideline was sent to a sample of experts in the field of lifestyle. Comments, mainly concerning clarification of text and terminology, were discussed and the text was adapted.

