#### Measurements

Questionnaires are sent to employees prior to the initial health risk appraisal. Questionnaires are collected by OPs or their assistants during the health risk appraisal. Biomedical measurements are performed by trained OPs or their assistants following a standard protocol. Follow-up measurements take place after 6, 12 and 18 months.

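### The long-term effect is set at 18 months but, as described, would be estimated as an average over 6, 12 and 18 months

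*Protocol article*

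**What the plan says.** All of the analysis text is in the Data analysis section under Phase 2 of the protocol article.

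- **Target.** Effectiveness will be "analyzed after 6 months (short term) and after 18 months (long term) by means of multilevel analyses". Short term is thus tied to 6 months and long term to 18 months.
- **Short-term analysis.** A two-level model (worker, occupational physician) with the 6-month value as outcome, adjusted for possible confounders such as gender, age and education. Of these the section adds: "These variables will also be checked for effect modification".
- **Long-term analysis.** "Long term data will be analyzed with three levels: 1. time (3 follow-up measurements at 6, 12 and 18 months"), with worker and occupational physician as the two higher levels. Then: "The long-term effect of the intervention will be analyzed using all three follow-up measurements (i.e. 6, 12 and 18 months) adjusted for possible confounders". A check of effect modification follows, with no variable named.

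Two other places fix the timing. The Measurements section says "Follow-up measurements take place after 6, 12 and 18 months". Step 4 of the guideline development places the last of the five counselling sessions "At the end of the intervention period after 6 months". The first follow-up therefore falls at the end of counselling.

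**The concern.** The section asks about the effect after 18 months and then describes an analysis that gives the three visits a single effect. Unless the treatment effect may differ by visit, the model returns one number for the whole of follow-up. One part of that number is the end-of-counselling value, which is already the entire short-term result.

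Counselling lasts 6 months and follow-up runs a further 12. The reason for the later visits is to learn whether an effect seen at 6 months is still there. A pooled coefficient cannot answer that: a steady 0.75 cm at every visit and a decline from 1.5 cm to nothing give the same value with complete data. A significant pooled result could be reported as a lasting effect when none is left at 18 months.

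**Working it through.** The plan gives no figure for this analysis, so there is none to reproduce. The check asks what the described model estimates when the effect fades.

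**Inputs from the protocol article**
- Difference of interest 1.5 cm, SD 4.5 cm, power 80%, alpha 5%, intraclass correlation 0.20, 175 workers per condition, 10 physicians per group, 20-40% loss by the final measurement (Sample size).
- Two-sided test; visits at 6, 12 and 18 months (Data analysis).

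**Assumptions (not in the document)**
- True differences of 1.5, 0.75 and 0 cm at the three visits.
- Exchangeable within-worker correlation ρ of 0.5 to 0.8.
- Dropout that is monotone and equal in both arms, with retention of 95/87/80% or 90/75/60%. The final values match the 20% and 40% loss in the plan; the earlier ones are assumed.
- A model with time effects, one arm term and no arm-by-time term.

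**Step 1: complete data.** Each visit has equal weight, so the arm coefficient is (1.5 + 0.75 + 0)/3 = 0.75 cm.

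**Step 2: dropout.** A worker seen k times contributes 1/(1 + (k−1)ρ) to the weight of each visit attended. With retention r6, r12, r18:
- u18 = r18/(1 + 2ρ)
- u12 = (r12 − r18)/(1 + ρ) + u18
- u6 = (r6 − r12) + u12
- pooled effect = (1.5·u6 + 0.75·u12 + 0·u18)/(u6 + u12 + u18)

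A random intercept for physician, with the same dropout pattern in every practice, scales the three weights by a common factor and leaves the result unchanged.

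| Retention | ρ | u6 | u12 | u18 | Sum | Pooled effect (cm) |
|---|---|---|---|---|---|---|
| 95/87/80% | 0.5 | 0.527 | 0.447 | 0.400 | 1.373 | 0.82 |
| 95/87/80% | 0.8 | 0.427 | 0.347 | 0.308 | 1.081 | 0.83 |
| 90/75/60% | 0.5 | 0.550 | 0.400 | 0.300 | 1.250 | 0.90 |
| 90/75/60% | 0.8 | 0.464 | 0.314 | 0.231 | 1.009 | 0.92 |

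Worked case, third row: (1.5 × 0.550 + 0.75 × 0.400)/1.250 = 1.125/1.250 = 0.90. The 6-month visit carries 0.550/1.250 = 44% of the weight and the 18-month visit 0.300/1.250 = 24%.

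**Step 3: chance of a significant pooled result, complete data, ρ from 0.5 to 0.9.** Without clustering, the plan's inputs need 2 × (4.5 × (1.96 + 0.84)/1.5)² ≈ 142 per arm for 80% power. The stated 175 differs from this; that is a separate matter and does not bear on this point. The standard error of a single-visit difference is 4.5 × √(2/142) = 0.534 cm, and that of the average is 0.534 × √((1 + 2ρ)/3).
- ρ = 0.5: 0.436 cm; 0.75/0.436 = 1.72; probability 0.41.
- ρ = 0.9: 0.516 cm; 0.75/0.516 = 1.45; probability 0.31.

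For 175 workers under 10 physicians the design effect is 1 + (17.5 − 1) × 0.20 = 4.3, and the effective number is 175/4.3 = 40.7 per arm. Applying that design effect to the average as to a single visit gives probabilities of 0.15 (ρ = 0.5) to 0.12 (ρ = 0.9). An 18-month contrast would be significant with probability 0.05, because the true 18-month effect is 0.

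**The case against.** The strongest reply is that the section lists data, levels and adjustment but not the fixed effects. Calling the lowest level time only marks the measurement occasions; it does not rule out time as a fixed effect or an interaction with arm. The quoted sentence fits a model with an arm-by-time term, and an article may leave such detail to a fuller plan. The 18-month phrase might also describe the period covered rather than one visit, and an average over follow-up is a legitimate estimand.

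Part of this stands. The single coefficient is the plain reading, not a statement in the text. It does not remove the point, because the article does describe the long-term analysis, and that description does not match the question set at the start of the same section. The modifiers it names are gender, age and education, not time. The later unspecified check of effect modification does not commit to an 18-month contrast.

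A reader might be tempted to go further in three ways that the document does not support.
- **That the economic evaluation rests on the wrong effect.** The Economic evaluation section has an 18-month horizon and its own bootstrap methods. Nothing there says that the waist difference comes from this model.
- **That the 6-month model is a completers-only analysis.** The section places all statistical analyses under intention to treat and states no such restriction.
- **That the authors themselves expect the effect to be lost.** The Background remark on regained weight concerns individual treatment of overweight people. It is set against prevention through small changes, which the authors consider easier to maintain. Step 4 also recommends continuing attention to relapse after the counselling.

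**Conclusion.** The point holds as a mismatch between the stated target and the described estimator. Followed as written, the plan gives a 6-18-month average under the name of an 18-month effect, and includes the short-term result in it. In the illustration, a true 18-month effect of 0 appears as 0.75 cm with complete data and as 0.82 to 0.92 cm with 20-40% loss. The probability of a significant result is then about 0.31 to 0.41 on the unclustered 80%-power basis, or 0.12 to 0.15 with the stated intraclass correlation, instead of 0.05.

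These sizes rest on the assumed decay, correlations and visit-level retention, and on a model without an arm-by-time term. They show what the analysis could hide and do not predict what the trial will find. If the investigators already intend an arm-by-time term and an 18-month contrast, one sentence saying so settles the matter.

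**What to change.** Keep the three-level model on all follow-up visits. Add time as a categorical fixed effect and an arm-by-time interaction, and name the 18-month contrast as the long-term effect. Report the average over 6 to 18 months, if wanted, only as a supplementary estimate under that label.

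This changes the analysis wording only; no visits or data are added. The price is precision: with complete data the 18-month interval is wider than that of the average by a factor of √(3/(1 + 2ρ)), which is 1.22 at ρ = 0.5 and 1.07 at ρ = 0.8. The gap grows with dropout.

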### Phase 2. Evaluation of the weight gain prevention guideline

The guideline is currently evaluated in a randomised controlled trial among 20 OPs including approximately 600 employees. Phase 2 describes the design of this trial, population, sample size and outcome measures, as well as a plan for adoption, implementation and evaluation (Step 5 and 6 of the IM protocol).

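### The arm effect rests on 20 OPs or fewer, and the Data analysis section names no small-sample method; a normal-reference test would exceed the stated 5% level

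*Protocol article*

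**What the plan says.** The introduction to Phase 2 describes a "randomised controlled trial among 20 OPs including approximately 600 employees". The Sample size section plans "approximately 300 workers among 10 OPs in each study group". For clustering it says "we adjusted for dependence of measurements with an intraclass correlation of 0.20". The size is set "Taking a loss to follow-up of 20-40% into account among workers and OPs until the final measurement".

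The Data analysis section recognises the unit of randomisation: "Due to randomization at the OP level, short term data will be analyzed with two levels: 1. worker and 2. OP". The long-term analysis adds measurement occasion as a third level below worker and OP. On the test it says "A two tailed significance level of p < 0.05 is considered statistically significant". The software is SPSS 15.0 and "MLwiN for multilevel statistical analyses".

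The article does not say whether the models are fitted by full or restricted likelihood. It also does not say which reference distribution or degrees of freedom apply to the arm effect.

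**The concern.** All workers of one OP are in the same arm, so the arm effect varies only between OPs. Its standard error depends on a between-OP variance estimated from few clusters. A large-sample multilevel test can then go wrong in two ways:

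- Full maximum likelihood divides the between-OP sum of squares by the number of OPs and ignores the two arm means already fitted, so the standard error is too small.
- A normal reference uses 1.96 where the t distribution requires about 2.10 (20 OPs) to 2.23 (12 OPs).

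Both errors shorten confidence intervals and raise the false-positive rate above the stated 5%. The trial's result feeds into adapting the guideline and, after authorisation, disseminating it nationally. The same arm contrast is also used for several primary outcomes and many secondary ones.

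**Working it through.** **Inputs from the article.** 20 OPs, 10 per arm; 300/10 = 30 workers per OP; ICC 0.20; loss 20-40%; two-sided alpha 0.05.

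**Assumptions that are not in the article.** Wald tests read against a normal distribution, with either ML or REML as estimator. Also, the 20-40% loss is applied to OPs, which leaves 20 x 0.8 = 16 or 20 x 0.6 = 12.

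**The plan's own figure.** On this point it is the 5% level. The 175 workers per condition does not enter the calculation.

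**Closed form.** With k OPs of equal size and a between-OP variance estimate away from zero, the arm effect divided by its REML standard error follows a t distribution on k - 2 df. The ML standard error is smaller by a factor sqrt((k - 2)/k). Hence

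- error with REML and 1.96: 2 x P(t_(k-2) > 1.96)
- error with ML and 1.96: 2 x P(t_(k-2) > 1.96 x sqrt((k - 2)/k))

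| OPs (k) | df | 1.96 x sqrt(df/k) | REML, normal | ML, normal | t critical value |
|---|---|---|---|---|---|
| 20 | 18 | 1.859 | 6.6% | 7.9% | 2.10 |
| 16 | 14 | 1.833 | 7.0% | 8.8% | 2.14 |
| 12 | 10 | 1.789 | 7.8% | 10.4% | 2.23 |

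**Simulation.** Null trials from a two-level random-intercept model, ICC 0.20, 18-30 workers per OP, equal and unequal OP sizes (coefficient of variation 0.5), 6,000 trials per setting. The Monte Carlo standard error is about sqrt(0.05 x 0.95/6000) = 0.3 percentage points.

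| OPs | REML, normal | ML, normal | REML, t on k - 2 | ML, t on k - 2 |
|---|---|---|---|---|
| 20 | 6.2-6.5% | 7.7-8.7% | 4.5-5.1% | 6.1-6.8% |
| 16 | 6.7-7.0% | 8.9-9.1% | 4.8-5.0% | 6.4-6.8% |
| 12 | 7.4-8.3% | 9.9-11.6% | 4.5-5.2% | 6.8-7.9% |

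A longer run for equal OP sizes (400,000 null trials per setting) agrees with the closed form to within 0.1 percentage point, so the closed-form values are the better summary.

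**Which part matters.** REML with t on k - 2 df holds about 5%. ML with the same t reference still gives about 6-8%. Both the estimator and the reference distribution therefore need to be fixed.

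**Dependence on the ICC.** With a normal reference, the simulated error is 6.0-9.6% at ICC 0.05 and 5.1-7.1% at ICC 0.01. At 0.01, REML with t on k - 2 df falls to about 3-4%, because the between-OP variance is often estimated as zero.

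**Interval width after the change.**

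- Relative to REML with 1.96: 2.10/1.96 = 1.07 with 20 OPs, and 2.23/1.96 = 1.14 with 12.
- Relative to ML with 1.96: 1.07 x sqrt(20/18) = 1.13 with 20 OPs, and 1.14 x sqrt(12/10) = 1.25 with 12.

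**The case against.** The strongest reply is that the fault is not in the text. The article names no Wald test, no normal reference and no estimator, and the name of a software package does not settle any of them. A journal article commonly leaves such details to a full protocol or analysis plan, which is not shown here. The article does take the main precaution by modelling OP as a level in both analyses. All of this stands, and the silence alone is not counted as an error.

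Three further limits also stand:

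- The loss is stated up to the final measurement and as one range for workers and OPs together. The count of 12-16 OPs is therefore one reading, and it belongs to the 18-month analysis. At 6 months the number may be close to 20, where REML with a normal reference gives only about 6.5%.
- The figure of 10% needs ML and 12 OPs together.
- The ICC of 0.20 is a planning value given for waist circumference only. It cannot be carried over to every outcome.

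What the reply does not remove is that the article's own figures (20 OPs, ICC 0.20, expected loss of OPs) put the trial where the choice of estimator and reference distribution decides whether the stated level is met. The section already fixes the levels of the model, the software, the sidedness and the alpha, so this choice belongs beside them.

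**Conclusion.** The point holds in conditional form, as an inexpensive improvement. If the arm effect is tested by a Wald statistic against a normal distribution, the two-sided error at ICC 0.20 would be about 6.5% (REML) to 8% (ML) with 20 OPs. With 12 OPs it would be about 8% to 10%. The excess shrinks as the ICC falls and is small at 0.01.

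A reader might infer that the planned tests do run at 7-10%, and for all outcomes. The article does not support that, because it never specifies the normal reference or the estimator and gives an ICC for one outcome only.

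The figures come from a two-level model without covariates. For the three-level long-term model they are a guide, since an arm effect averaged over follow-up is still a contrast between OPs.

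**What to change.** In the Data analysis section, state that the multilevel models are fitted by restricted likelihood (RIGLS/REML). State also that tests and confidence intervals for the arm effect use a t distribution on (analysed OPs - 2) df, or an equivalent method such as Satterthwaite or Kenward-Roger df. A permutation test over OP labels can serve as a check. If a fuller plan already says this, a cross-reference is enough.

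The change needs no new data and no change of design, and should be settled before unblinding. Its price is wider intervals, by the 7-14% or 13-25% shown above depending on the starting point. There is also some conservatism for outcomes with a very low ICC.
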